## Abstract

**Background:**

After stroke, pneumonia is a relevant medical complication that can be precipitated by aspiration of saliva, liquids, or solid food. Swallowing difficulty and aspiration occur in a significant proportion of stroke survivors. Cough, an important mechanism protecting the lungs from inhaled materials, can be impaired in stroke survivors, and the likely cause for this impairment is central weakness of the respiratory musculature. Thus, respiratory muscle training in acute stroke may be useful in the recovery of respiratory muscle and cough function, and may thereby reduce the risk of pneumonia. The present study is a pilot study, aimed at investigating the validity and feasibility of this approach by exploring effect size, safety, and patient acceptability of the intervention.

**Methods/design:**

Adults with moderate to severe stroke impairment (National Institutes of Health Stroke Scale (NIHSS) score 5 to 25 at the time of admission) are recruited within 2 weeks of stroke onset. Participants must be able to perform voluntary respiratory maneuvers. Excluded are patients with increased intracranial pressure, uncontrolled hypertension, neuromuscular conditions other than stroke, medical history of asthma or chronic obstructive pulmonary disease, and recent cardiac events. Participants are randomized to receive inspiratory, expiratory, or sham respiratory training over a 4-week period, by using commercially available threshold resistance devices. Participants and caregivers, but not study investigators, are blind to treatment allocation. All participants receive medical care and stroke rehabilitation according to the usual standard of care. The following assessments are conducted at baseline, 4 weeks, and 12 weeks: Voluntary and reflex cough flow measurements, forced spirometry, respiratory muscle strength tests, incidence of pneumonia, assessments of safety parameters, and self-reported activity of daily living. The primary outcome is peak expiratory cough flow of voluntary cough, a parameter indicating the effectiveness of cough. Secondary outcomes are incidence of pneumonia, peak expiratory cough flow of reflex cough, and maximum inspiratory and expiratory mouth pressures.

**Discussion:**

Various novel pharmacologic and nonpharmacologic approaches for preventing stroke-associated pneumonia are currently being researched. This study investigates a novel strategy based on an exercise intervention for cough rehabilitation.

**Trial registration:**

Current Controlled Trials ISRCTN40298220

## Background

### Stroke-associated pneumonia

Pneumonia is a well-reported medical complication after stroke, in particular within the first weeks and months after the event. A recent review
[1] identified 54 published studies reporting the incidence of pneumonia after stroke. These publications span from 1998 to 2012 and present data from intensive care, acute, and rehabilitation settings. The reported incidence of pneumonia is highest in intensive care patients (median, 27%; range, 4.1% to 56.6%), although ventilator-associated pneumonia may be a confounding factor in this setting. For acute stroke units, general medical wards, and rehabilitation units, the reported incidence of pneumonia ranges from 3.9% to 45%, with a median incidence rate of 7.4%. Studies differ in the criteria for the diagnosis of pneumonia, characteristics of study samples, and time periods of observation, and it may not be appropriate to compare studies directly. The most current and valid data available for the United Kingdom (UK) is from the national stroke audit for England, Wales, and Northern Ireland, which showed incidence rates of 16% in 2008
[2] and 13% in 2010
[3].

Pneumonia after stroke is associated with worse patient outcomes. Patients in whom pneumonia develops have an estimated twofold to sixfold increase in risk of death
[4-15], are approximately 3 to 6 times more likely to have poor scores on various rehabilitation measures
[6,7,11,12,16], stay in the acute hospital on average for 3 times longer than those without pneumonia, and also require higher levels of care after hospital discharge
[4,7,9,12,14,17,18].

Swallowing difficulty (dysphagia) is one of the most frequently identified predictors of poststroke pneumonia
[1,7,13,19-23]. Dysphagia is common in stroke, with an average incidence rate of 40%
[24], although reported figures vary (14% to 94%) because of differences in sample selection and method and timing of swallow assessments
[23,25-28]. Dysphagia is associated with an approximately twofold to threefold increase in risk of developing poststroke pneumonia
[7,13,19-23]. This risk increases to fivefold to 11-fold with worsening severity of swallowing difficulty, the presence of aspiration (material entering the trachea past the vocal cords), and worsening severity of aspiration
[23,29-31]. Several studies highlight the risk posed by silent aspiration (aspiration that occurs without triggering a protective cough) and the protection cough provides from aspiration pneumonia
[32-34]. Some studies also demonstrate the association between weak or absent cough and higher incidence of aspiration in stroke survivors
[35,36].

### Strategies for preventing stroke-associated pneumonia

To date, the single most successful strategy to prevent poststroke pneumonia has been the early detection of swallowing difficulty through routine swallow screening, followed by implementation of dysphagia-management strategies
[1,9,21,37]. Various approaches to further reduce poststroke pneumonia rates are currently being researched. Pharmacologic approaches include the preventive administration of antibiotics
[1,38], the use of ACE inhibitors to improve reflex cough sensitivity
[39], and approaches targeting stroke-induced immunodepression
[1]. Nonpharmacologic strategies include elevated body positioning to prevent aspiration
[39] and reduction of oropharyngeal pathogens through intensive oral hygiene
[1,39]. The present study investigates a novel nonpharmacologic approach, by using respiratory muscle training (RMT) to improve cough effectiveness and airway protection in acute stroke patients.

### Cough impairment in acute stroke

Cough is an important mechanism to protect from aspiration. It requires the coordinated activation of respiratory muscles (inspiratory and expiratory) and intrinsic laryngeal muscles. In a cough maneuver, inspiratory muscle action first causes air to be drawn into the lungs. Expiratory muscle contraction then creates a buildup of intrathoracic pressure against a closed glottis. Finally, a blast of air is released by rapid glottis opening, producing the characteristic cough sound and moving particles from the lungs toward and into the pharynx
[40].

Stroke can adversely affect cough function. Peak expiratory cough flow (PECF), a measure of cough effectiveness, was found to be reduced by approximately one third in acute and chronic stroke patients when compared with healthy elderly subjects and normative values
[41,42]. In detailed physiological studies of cough and respiratory muscle function, acute stroke patients were compared with matched healthy control subjects
[43,44]. It was found that parameters of respiratory muscle strength (maximum inspiratory and expiratory mouth pressures, sniff pressure) and cough (PECF, gastric pressure during cough) in stroke subjects were reduced by one third to one half. This was demonstrated in voluntary and reflex cough. No difference between stroke and control subjects was found in the function of the intrinsic laryngeal muscles (glottis-closure phase during cough); or in respiratory muscle function when muscles were stimulated peripherally
[43,44].

These findings demonstrate that a significant impairment of cough and respiratory muscle function occurs in acute stroke; that the impairment of cough function is likely related to respiratory muscle weakness, as opposed to dysfunction at the level of the glottis; and that the respiratory muscle weakness is related to the central component of the motor pathway (that is, the stroke lesion). Thus, an intervention targeting stroke-induced central respiratory muscle weakness may improve cough effectiveness and reduce the risk of stroke-associated pneumonia.

### Respiratory muscle training in stroke

Respiratory muscle training (RMT) aims to improve respiratory performance by loading the respiratory system beyond its usual level of functioning, thereby creating a training effect
[45-48]. Much research on RMT has been conducted in healthy subjects, in athletes, and in clinical populations with primary respiratory problems. A small number of studies have investigated RMT in groups with neurologic conditions
[49]. Two randomized controlled trials of inspiratory muscle training by using the threshold loading technique were conducted in chronic and subacute stroke patients
[49-52]. Both trials demonstrated statistically significant improvements in inspiratory muscle strength and other physiological parameters for the RMT groups. Although the observed effect sizes were modest in absolute terms, these studies provide proof of principle that physiological improvement in stroke survivors is achievable through RMT.

### Aims and objectives

The present study investigates whether RMT is a worthwhile treatment approach to pursue for the reduction of pneumonia rates in acute stroke patients. The aim is to provide estimates on its magnitude of effect, acceptability, safety, and feasibility, and to inform about the value and design of a large clinical trial. The study objectives are (a) to determine the magnitude of effect of the intervention on cough generation, respiratory muscle strength, and incidence of pneumonia; (b) to explore the training duration, frequency, and intensity required to achieve improvement in cough flow and inspiratory and expiratory muscle strength; (c) to evaluate patient participation, acceptability of study procedures to participants, and concordance with training protocol; (d) to describe safety parameters and potential adverse effects of RMT in this patient group; (e) to describe characteristics of those patients most likely to gain from the intervention; and (f) to determine the relevance and feasibility of delivering RMT to acute stroke patients in a National Health Service (NHS) setting in the United Kingdom (UK).

## Methods/design

### Study design

The study is a pilot study, designed as a single-blind randomized controlled trial with three study groups. Participants are randomized to receive inspiratory muscle training, expiratory muscle training, or sham RMT. After the baseline assessment, participants undergo a 4-week intervention period. Weekly investigator visits are conducted during the intervention period. The primary study end point is at the end of the intervention period (day 29). A final reassessment is conducted at 12 weeks after baseline. One investigator conducts all study procedures, including screening for eligibility, gaining consent, conducting study assessments, and introducing and assisting with the intervention. A summary of the study timeline and all data collected is given in Additional file
1. The participant flow through the study is described in Figure 
1.

**Figure 1 F1:**
[figure not shown]
Flowchart of study design.

### Study setting

Acute stroke patients are screened for eligibility at one Hyperacute Stroke Unit (HASU) at one tertiary center in London, UK. Participants receive medical care and stroke rehabilitation according to the current standard of care. During the study period, participants may be discharged home or transferred to specialized stroke-rehabilitation units within the geographic area.

### Participants

The population of interest for this study comprises all patients admitted to hospital with an acute stroke, except for those with very mild stroke symptoms or without weakness. The inclusion and exclusion criteria reflect the nature of the study procedures, which require the participant to carry out volitional respiratory maneuvers with adequate technique; and the potential vulnerability of this acute patient group to extreme changes in intrathoracic pressures, which may be caused by respiratory maneuvers.

Inclusion criteria for the study are as follows:

– Age 18+ years

– Confirmed medical diagnosis of acute stroke (ischemic or hemorrhagic)

– Moderate to severe stroke impairment, defined as National Institutes of Health Stroke Scale (NIHSS)
[53] score 5 to 25 and stroke-related weakness at the time of admission

– Within 2 weeks of stroke onset

– Ability to follow instructions and engage in study procedures

– Ability to give informed consent

Exclusion criteria are as follows:

– Signs of increased intracranial pressure on computed tomography (CT) scan

– Poorly controlled hypertension, defined as blood pressure higher than 180/100 at three or more occasions over the preceding 24 hours

– Myocardial infarction, angina, or acute heart failure in the preceding 3 months

– Pulmonary, neurologic (other than stroke), or orthopedic conditions adversely affecting the respiratory pump, including asthma and chronic obstructive pulmonary disease (COPD)

### Informed consent and ethical approval

Eligible patients are approached and invited to take part in the study. The study purpose and procedures are explained, taking into account any communication difficulties caused by the stroke. A study information sheet is provided. Patients are given at least 24 hours to consider the study. Only patients who have the ability to give informed consent are eligible. Patients who are willing to take part sign a written consent form. The study was granted ethical approval from the UK National Research Ethics Service (NRES) (Wandsworth Research Ethics Committee, study reference 10/H0803/32).

### Randomization, blinding, and treatment allocation

Sequentially numbered sealed envelopes containing the treatment allocation were prepared by a researcher unrelated to the study team. The randomization sequence was computer-generated. Block randomization (blocks of 12, containing four participants per study arm) was used to ensure even participant spread across the trial groups.

For each participant, the investigator opens the respective envelope after informed consent has been gained and immediately before conducting the study baseline session. Thereafter, the investigator is aware of the participant’s group allocation. Participants, caregivers, and healthcare professionals are unaware of group allocation throughout the study period.

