### Weaknesses

The methods for identifying the presence of swallowing difficulty and pneumonia in the current study may be regarded as a limitation. To minimize participant burden created by additional medical procedures, it was decided to take a pragmatic approach and observe clinical and self-reported information on swallowing function and pneumonia. A more-detailed instrumental assessment of swallowing, such as video-fluoroscopic examination of swallow, could be used to determine the degree of dysphagia and aspiration. Objective diagnostic criteria for pneumonia, including assessments of chest radiographs and blood results
[69,70], could be used to support the detection of pneumonia.

A further limitation to the study is the lack of investigator blinding. The investigator is masked to treatment-allocation sequence, but is aware of group allocation from the point of randomization.

Although the clinical purpose of this research is to reduce the risk of pneumonia after stroke, the study uses voluntary cough flow as a surrogate primary outcome. This surrogate outcome was selected to minimize the required sample size. Designing the study according to the primary outcome, pneumonia, would require a considerably larger sample. For example, it could be assumed that both intervention groups would show a reduction in pneumonia rates from 15% to 7.5% compared with the control group. To give 80% power at the 5% significance level, this would require approximately 180 participants per group (using the χ^2^ test and not accounting for attrition).

The choice of voluntary cough flow as a surrogate primary outcome in this study was based on the physiological rationale to the research. Also, good evidence shows that reduced voluntary cough flow in stroke patients is associated with higher risk of aspiration, and therefore aspiration pneumonia
[35,36]. To our knowledge, the direct relation between voluntary cough flow and pneumonia has not been investigated in stroke populations. The importance of cough flow may be inferred from populations with neuromuscular conditions, where reduced levels of voluntary cough flow indicate the need for assisted airway clearance

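### With one fixed block of 12 and a single unblinded recruiter, allocations near the end of each block can be deduced, so the unqualified claim of masking to the sequence is wrong as written

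*Protocol article*

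**What the plan says.** Under Randomization, blinding, and treatment allocation, the Protocol article gives a single block size: "Block randomization (blocks of 12, containing four participants per study arm) was used to ensure even participant spread across the trial groups". The concealment device is described there as well: "Sequentially numbered sealed envelopes containing the treatment allocation were prepared by a researcher unrelated to the study team". For each participant, "the investigator opens the respective envelope after informed consent has been gained and immediately before conducting the study baseline session", and the next sentence adds "Thereafter, the investigator is aware of the participant’s group allocation".

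Under Study design: "One investigator conducts all study procedures, including screening for eligibility, gaining consent, conducting study assessments, and introducing and assisting with the intervention". Under Study setting, screening takes place at one unit. No stratification is described, so I assume one running sequence.

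Under Weaknesses, the lack of investigator blinding is acknowledged, but with this assurance: "The investigator is masked to treatment-allocation sequence, but is aware of group allocation from the point of randomization". Trial status shows that recruitment was still open when the article, with its block size, was written.

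**The concern.** A sealed envelope hides the card inside it. It does not hide an allocation that follows by subtraction from those already opened. With a fixed 4/4/4 block, the last place is always determined by the first eleven, and earlier places often become more predictable as arms fill up. The person who could do this subtraction is the person who decides whom to approach and when.

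The opportunity to act on it is real. Entry depends partly on that investigator's judgement ("Ability to follow instructions and engage in study procedures"), and the two-week window from stroke onset leaves some room to time an approach. The primary outcome, voluntary cough PECF, comes from repeated maximal efforts, so it depends directly on strength and cooperation. Baseline PECF is not among the ANCOVA covariates listed under Statistical analysis, so a baseline difference in cough strength between arms would not be adjusted for directly. Selection of this kind acts before consent, and a blinded outcome assessor would not remove it.

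**Working it through.** **Inputs.** Block of 12, four per arm, three arms (Randomization section). One sequence and one recruiter who sees every past allocation (Study setting, Study design, Randomization). Revised target of 90, with early stopping once 20 per group complete the primary end point (Sample size). Assumption: the recruiter knows the block size and keeps a tally. The plan gives no predictability figure of its own to reproduce.

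**Allocations certain in advance.** An allocation is certain when only one arm has places left, that is, in the final run of a single arm. For a given arm, each of its 4 members falls with equal probability into one of the 9 gaps formed by the other 8 places. The expected number after the last of those 8 is therefore 4/9. Over three arms: 3 × 4/9 = 4/3 = 1.33 per block, and 1.33/12 = 11.1%.

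**Sham versus active settled.** This happens when sham is used up or only sham is left.
- Sham used up: each of the 8 active places falls into one of 5 gaps around the 4 sham places, so 8/5 = 1.600.
- Only sham left: 4/9 = 0.444.
- Sum: 2.044 per block, or 17.0%.

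**Best guess.** Guess the arm with most places left. With remaining counts (a, b, c) and t = a + b + c, the expected number of correct guesses is G(a,b,c) = max(a,b,c)/t + Σ (x/t) × G(counts after one x is used), where x runs over a, b and c. This gives G(4,4,4) = 4731/770 = 6.144 of 12, or 51.2%. Chance is 33.3%.

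**Scaling to 90.** This is 7 full blocks plus the first six places of an eighth.
- Certain: none is possible in the first six places, so 7 × 1.333 = 9.3 (10.4%).
- Sham versus active: in the half block, all four sham places fall in the first four with probability 1/495, and in the first five with probability 5/495. That adds 6/495 = 0.012. Total 7 × 2.044 + 0.012 = 14.3.
- Best guess: the half block gives 2.395, so 7 × 6.144 + 2.395 = 45.4 correct (50.4%).

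Ninety is a ceiling. If nobody dropped out and recruitment stopped at 60 (five blocks), the certain allocations would be 5 × 1.333 = 6.7.

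**Effect of varied blocks.** I simulated sequences of 90 with block sizes drawn at random from 6, 9 and 12, and a recruiter who knows that set of sizes but not their order. About 2.4% of allocations are certain, against 10.4% under the fixed block. Best-guess accuracy is about 52%, so varying the sizes removes most of the certainty but not the guessing advantage.

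**The case against.** The strongest reply is that the usual safeguards are in place. Someone outside the study team prepared the list, the envelopes are sealed and numbered, and each is opened only after consent. About 8 in 9 allocations are not certain even to a recruiter who counts. Twelve is not a small block, the lack of investigator blinding is already disclosed, and this is a pilot. All of that stands as mitigation. It does not rescue the unqualified masking statement, because the last place of every fixed block is deducible. Nor does pilot status settle it: the stated aims include estimating the magnitude of effect to inform a large trial.

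Three stronger readings are tempting, and the article does not support them.

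- A reader might infer that one allocation in nine was in fact known. The article does not say that the recruiter knew the block size or kept a tally. Printing it during recruitment makes the knowledge plausible from then on, not for earlier participants. Equally, nothing says that the size was withheld.
- A reader might infer that masking failed altogether. It is incomplete.
- A reader might infer that selection bias occurred. The figures measure predictability, not bias in PECF, and no evidence of selective approach is given.

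A reader might also prefer simple randomisation for the remaining participants, which would bring guessing down to 33%. That is a debatable trade. With 30% dropout and 90 participants, the chance that every arm reaches 20 completers is about 39% with 30 per arm. It falls to about 25% if the last 42 are allocated without blocks. The number remaining is not stated; with 30 or 54 remaining, the figure is about 28% or 22–23%.

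**Conclusion.** The point holds in a conditional form. For an investigator who knows the block size and tallies past allocations, 11% of allocations per complete block are deducible, sham versus active is settled in 17%, and the best guess is right 51% of the time. Over 90 participants that is at most 9.3 certain allocations and 14.3 with sham versus active known. The results rest on a single unstratified sequence and on knowledge of the block size, which the article does not state but does make available during recruitment. The masking sentence under Weaknesses claims more than the design delivers and should be corrected. The size of any resulting bias in the treatment comparison cannot be derived from the article.

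**What to change.** 1. Have the unrelated researcher replace the unused envelopes with a new computer-generated list in randomly varied block sizes. Withhold the sizes from the recruiting investigator and do not publish them until recruitment closes. Sizes 6, 9 and 12 are one example that keeps the arms closely balanced. The cost is one re-run of the list and a new set of envelopes. The remaining weakness is a guessing advantage near 52%.

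2. Amend the masking sentence under Weaknesses. It should say that the envelopes conceal each allocation until consent, but that allocations near the end of a fixed block of 12 could be deduced by the unblinded recruiter. Give details of any new list only after recruitment closes, so that the correction does not disclose it. The cost is a change of wording.

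3. In the study report, compare by arm the baseline characteristics, including baseline voluntary cough PECF, of participants in the last places of each fixed block with those of the others. This uses data already collected. The numbers will be small, so the comparison is descriptive and cannot rule selection out.

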For the off-site system, a different analog-to-digital converter (NI BNC-2110; National Instruments, Newbury, England) and laptop with data-acquisition software (LabView, version 5.1, National Instruments) are used. The on-site and off-site systems have the same performance characteristics: linear response from zero to 700 L/min in both directions of flow; frequency response of >20 Hz; and analog-to-digital sampling of 2 kHz. The systems are calibrated before each testing session by two-point calibration with a rotameter (InFlux OF1”S, 60 to 600 L/min flow; Techniquip Ltd, Taunton, England) at a reference flow of 500 L/min.

Voluntary and reflex coughs are assessed. For voluntary coughs, participants make repeated maximal cough efforts into a tight-fitting face mask, until five coughs of similar PECF are recorded. To elicit reflex coughs, escalating concentrations of capsaicin (0.49 to 1,000 μ*M*) are nebulized (UltraNeb U3000; DeVilbiss Healthcare Ltd, Tipton, England) and introduced into the face mask for 1 minute at a time, until the threshold is reached at which five bouts of reflex coughing are triggered. From the recorded cough-flow traces, the following parameters are derived for the five voluntary and five reflex coughs with the highest peak expiratory flow rates: peak expiratory cough flow (PECF), peak inspiratory cough flow (PICF), volume expired (VE), volume inspired (VI), glottis compression time, and cough-volume acceleration.

To monitor the safety of the intervention, blood pressure, heart rate, and blood oxygen saturation are measured before and after participants carry out RMT. Measurements are made by using a digital blood pressure monitor (UA-767 Plus; A&D Instruments Ltd, Abingdon, Oxon, UK) and a finger pulse oximeter (Onyx 9500; Nonin Medical Inc, Plymouth, MN, USA). In addition, the investigator notes any subjective discomfort reported during training. Adverse events are noted and reviewed throughout the duration of the study.

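### The arm is revealed to the sole assessor before the effort-dependent baseline cough, mouth-pressure and spirometry tests, although it is not needed until the training device is set up

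*Protocol article*

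**What the plan says.** All references are to the protocol article.

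- **When the arm becomes known.** Under Randomization, blinding, and treatment allocation: "the investigator opens the respective envelope after informed consent has been gained and immediately before conducting the study baseline session". The text continues: "Thereafter, the investigator is aware of the participant’s group allocation".
- **Who measures.** Under Study design: "One investigator conducts all study procedures, including screening for eligibility, gaining consent, conducting study assessments, and introducing and assisting with the intervention".
- **What is measured at baseline.** In the Abstract, under Methods/design: "The following assessments are conducted at baseline, 4 weeks, and 12 weeks: Voluntary and reflex cough flow measurements, forced spirometry, respiratory muscle strength tests".
- **How far the tests depend on the participant and the tester.** Under Participants, the study procedures are said to "require the participant to carry out volitional respiratory maneuvers with adequate technique". For voluntary cough, Study parameters says that "participants make repeated maximal cough efforts into a tight-fitting face mask, until five coughs of similar PECF are recorded". The analysed values come from the five coughs with the highest peak flow. The article gives no tolerance for similarity and no maximum number of attempts.
- **What needs the arm.** The Intervention section names three steps: the choice of device, its resistance (a percentage of the participant's own maximum mouth pressure) and instruction in technique, which is given in the baseline session. Mouth pressures are measured again each week and the resistance is adjusted.
- **What is disclosed.** Under Weaknesses: "The investigator is masked to treatment-allocation sequence, but is aware of group allocation from the point of randomization". That section does not say that the baseline measurements are affected.

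**The concern.** A baseline value is useful in a randomized trial because the allocation cannot have influenced it. Here it can. The person who encourages the participant, judges when five coughs are alike enough and decides when to stop already knows whether the participant will receive inspiratory, expiratory or sham training. Any unconscious difference in encouragement or persistence between arms would appear as a baseline difference that randomization did not produce, and the data could not distinguish it from chance imbalance.

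The article plans to use baseline values in three ways. They describe the groups at the start. They replace missing day-29 values in one of four missing-data approaches. Baseline mouth pressure also fixes the first training resistance. Each inherits whatever knowledge of the arm has added to the measurement.

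**Working it through.** The article states no figure on this point, so there is none to reproduce. The check has two parts.

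**1. Order of events**

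1. Consent is obtained, the envelope is opened, and the baseline session follows (Randomization section).
2. The person who opens the envelope is the one who does all assessments (Study design).
3. Cough flow, spirometry and respiratory muscle strength are measured at baseline (Abstract). Nothing shown says that they are completed before the envelope is opened.
4. Both MIP and MEP are outcomes compared between groups, so both are needed at baseline in every arm. The arm is not needed to decide what to measure.
5. The resistance is a percentage of maximum mouth pressure, so that pressure must be measured before the device can be set. The steps that need the arm therefore already come after the mouth-pressure measurement, and opening the envelope between the two fits the existing session.

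**2. Size of the effect where baseline enters the analysis**

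Inputs:
- *m*, the share of participants without a day-29 value. The Sample size section reports 32% attrition at the review after 40 participants, against 20% assumed initially. Applying 32% to day 29 in the affected arm is an assumption.
- *b*, the shift that knowledge of the arm causes in one arm's mean baseline PECF. The documents give no value, so 10, 25 and 50 L/min are assumed, with the same shift in participants who later drop out as in those who complete.

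Under baseline substitution, an arm's day-29 mean is (1 − m) × mean of observed day-29 values + m × mean baseline of those missing. If the second term is shifted by b, the arm mean moves by m × b.

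| Assumed b (L/min) | m = 0.20 | m = 0.32 |
|---|---|---|
| 10 | 0.20 × 10 = 2 | 0.32 × 10 = 3.2 |
| 25 | 0.20 × 25 = 5 | 0.32 × 25 = 8 |
| 50 | 0.20 × 50 = 10 | 0.32 × 50 = 16 |

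If the other arms are not shifted, the between-arm difference moves by the same amount. The sign follows the sign of b, which is unknown.

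For scale: the revised target of 90 gives 30 per arm. With the group SDs of about 100 to 250 L/min reported at the review, the standard error of a difference between two arms is SD × √(2/30) = 0.258 × SD, or about 26 to 65 L/min. This assumes that the SD is unchanged by substitution. The illustrated shifts all lie below one standard error.

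**Complete-case ANCOVA.** The listed covariates are gender, age, smoking, NIHSS score, training intensity and a missingness predictor. The compared quantity is the day-29 group mean. Baseline PECF is in neither place, so the direct shift is zero.

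**The case against.** The strongest reply is that little in the plan depends on baseline PECF. A reader might infer that the primary comparison is biased through adjustment for baseline or through change scores. The article does not support that: it compares day-29 means, lists no baseline PECF covariate and describes no change-from-baseline analysis. Baseline substitution is one of four approaches in a sensitivity comparison, and the training load is revised weekly, so baseline governs only its first setting. This stands, and it limits the size of the point.

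Second, the lack of investigator blinding is disclosed, and the larger exposure is the unblinded day-29 measurement, which reordering the baseline session does not touch. That also stands. But the disclosure treats unblinding as one undivided limitation. With one investigator, an unblinded day-29 test is hard to avoid; an unblinded baseline is not.

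Third, a reader might infer that the investigator who knows the arm also derives PECF from the recorded traces. Study parameters names nobody for that step, so it can only be an assumption. Reflex cough is provoked by capsaicin and is less volitional than the other tests. The requirement that five coughs be alike narrows the room for selecting high efforts, although without a stated tolerance or limit it does not close it.

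Finally, the timeline in Additional file 1 is not shown. Taking the baseline session to contain the baseline assessment follows from the Abstract, Study design and Intervention sections, and nothing shown contradicts it. Allocation remains hidden until consent, so this point concerns measurement, not who is recruited.

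**Conclusion.** The point holds as a defect in the order of steps. The sole assessor knows the arm before taking baseline voluntary cough, mouth-pressure and spirometry measurements, nothing in those measurements requires that knowledge, and the article's statement of limitations does not identify the consequence.

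Its reach in the plan as written is the baseline-substitution sensitivity analysis, the baseline description of the groups and the initial training load. For the first, the illustrated shift is about 3 to 16 L/min at 32% missing and 2 to 10 L/min at 20%, for assumed arm-specific baseline biases of 10 to 50 L/min. The documents contain no evidence that a bias of any particular size exists. The complete-case ANCOVA at day 29 carries no direct shift. The article does not say which variables enter the two model-based imputations, so no claim is made about them.

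**What to change.** 1. For remaining participants, open the envelope only after all baseline cough, spirometry and mouth-pressure measurements have been recorded, immediately before the device is set up.
2. Report how many participants had baseline taken after opening and how many before.
3. Derive PECF from the stored traces under coded file names that hide arm and visit. This also covers day 29 and traces already recorded, and it protects against the possibility, which the article leaves open, that the unblinded investigator does the derivation. It cannot remove differences in encouragement at the time of testing.

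The first change reorders steps within one session and needs no extra staff; the second is a count; the third is a file-renaming step. The small downside is that baseline procedures will differ between earlier and later participants, since 40 had already completed when the sample size was reviewed. The count in step 2 makes that visible. The disclosed limitation of unblinded assessment at day 29 remains and should stay in the report.
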